## Abstract

**Background:**

In patients with pulmonary embolism (PE), identifying predictors of recurrence is important to risk-stratify patients and tailor anticoagulation duration. After PE, a significant proportion of patients demonstrate residual pulmonary vascular obstruction (RPVO) on lung imaging. However, the exact prognostic significance of RPVO for venous thromboembolism recurrence remains unclear.

**Objectives:**

The primary objective is to assess whether RPVO on ventilation/perfusion (V/Q) single photon emission computed tomography (SPECT)/CT imaging after completion of 3 to 6 months of anticoagulation is an independent predictor of venous thromboembolism recurrence in patients with PE.

**Methods:**

The PRONOSPECT trial is a prospective multicenter cohort study. Participants are patients who experienced an objectively proven PE, provoked by a minor transient risk factor or unprovoked; who have been treated with anticoagulant therapy for 3 to 6 uninterrupted months; and for whom anticoagulation will not be prolonged. A standardized baseline patient assessment will be conducted including V/Q SPECT/CT imaging, collection of other potential predictor variables, and a functional evaluation. Anticoagulants will be withdrawn at the 3- or 6-month points from diagnosis and patients will be followed up for up to 2 years.

**Conclusion:**

The PRONOSPECT cohort study has the potential to determine whether the presence of RPVO on V/Q SPECT/CT imaging predicts the risk of recurrence in patients with PE in whom there remains a doubt on duration of anticoagulation.

## Introduction

1

### Background and rationale

1.1

#### Current approach to decide the duration of anticoagulation therapy in patients with pulmonary embolism

1.1.1

One of the main complications of pulmonary embolism (PE) is recurrence, which can be fatal in approximately 10% of cases [1]. Anticoagulant therapy is very effective in preventing recurrence, but this needs to be balanced against the risk of major bleeding. Current clinical practice guidelines recommend at least 3 to 6 months of oral anticoagulation therapy (OAT) after a first episode of venous thromboembolism (VTE) [2]. However, the benefit of OAT is not maintained after discontinuation of treatment [3]. Accordingly, the choice is between OAT of short and limited duration (3-6 months), and indefinite treatment.

Patients with PE can be stratified in 3 groups according to the risk of recurrence. Patients with a first episode of PE, which was provoked by a major transient risk factor (eg, major surgery), have a very low risk of recurrence after OAT discontinuation (<2% at 1 year); consequently, 3 months of OAT is recommended. In contrast, when PE occurred in patients with persistent major risk factors (eg, cancer) or in the absence of any transient (major or minor) risk factor, the risk of recurrence is high (>9% at 1 year) [4,5] and indefinite OAT is recommended [6]. Between these 2 phenotypes, the risk of recurrence is intermediate (4%-7%). This group includes PE provoked by a weak transient risk factors (eg, leg injury associated with reduced mobility and short admission to hospital with an acute illness). If prolonged anticoagulation is currently not recommended in this population [2,6], identifying patient subgroups at higher risk of recurrence remains an important clinical issue. As stated in a communication from the subcommittee on control of anticoagulation of the Scientific and Standardization Committee of the International Society on Thrombosis and Haemostasis (ISTH), a risk of recurrence of appreciably higher than 5% at 1 year and 15% at 5 years would not be acceptable to many physicians and would usually discourage stopping OAT after VTE [7]. Accordingly, identifying risk factors of recurrent PE remains a major interest in order to improve risk stratification of these patients at intermediate risk of recurrence. This could enable the identification of subgroups with lower risk in whom indefinite OAT should be avoided, as well as higher-risk patients who may require indefinite OAT.

#### Risk factors to predict VTE recurrence

1.1.2

Several clinical, biochemical, or imaging predictors of VTE recurrence have been identified, including age, male gender [8,9], obesity [10], some biologic thrombophilia [11,12], plasma D-dimer levels [13,14], or residual vein obstruction after deep vein thrombosis (DVT) [15]. However, the strength of the association with recurrent VTE was found to be moderate. Scores combining several risk factors have been proposed [[16], [17], [18], [19]], but they have been designed to determine the duration of treatment in patients with unprovoked PE, with an attempt to identify a subgroup of patients who would not require indefinite OAT. Predictors of recurrence in patients with provoked PE have been much less studied, and the challenge in this specific population would be to identify a subgroup of patients at higher risk who would benefit from long-term OAT.

#### Residual pulmonary vascular obstruction to predict the risk of VTE recurrence

1.1.3

Residual pulmonary vascular obstruction (RPVO) can be defined as an incomplete repermeabilization of the pulmonary arteries after acute PE. RPVO is found in approximately 30% to 40% of patients after a first episode of PE [20]. Several studies have assessed RPVO as a predictor of VTE recurrence [19,[21], [22], [23], [24], [25]]. Most studies suggested that the presence of RPVO identified via lung ventilation/perfusion (V/Q) scintigraphy after a minimum of 3 months of OAT might be associated with a 2- to 3-fold increased risk of recurrent VTE. In a recent systematic review and meta-analysis of individual participant data in 809 patients with PE who underwent lung planar scintigraphy after at least 3 months of anticoagulation, the risk of recurrent VTE at 1 year was 5.8% (4.4%-7.2%) in patients with RPVO of <5%, compared with 11.7% (9.5%-13.8%) in participants with RPVO of ≥5% [26]. Of note is that 80.6% of patients had unprovoked PE.

However, some studies have methodologic limitations eg, inclusion of patients in long-term anticoagulation or unblinded use of V/Q scintigraphy for patients’ management. There is heterogeneity of studies in terms of population, VTE recurrence rate, or RPVO definition. The prognostic impact of RPVO was mostly reported in patients with unprovoked PE, for whom long-term anticoagulation is now recommended. There is limited data available on patients at an intermediate risk of recurrence. Finally, RPVO index was assessed in most of studies with V/Q planar scintigraphy while V/Q SPECT/CT imaging is currently widely used in daily practice.

#### Why using V/Q SPECT/CT imaging to assess RPVO?

1.1.4

Most studies that assessed RPVO as a predictor of VTE recurrence used V/Q planar scintigraphy rather than computed tomography pulmonary angiography (CTPA) [27]. CTPA and V/Q scintigraphy rely on different approaches. CTPA provides morphologic information (partial or complete obstruction of a pulmonary artery branch), whereas V/Q scintigraphy shows functional consequences of PE on the regional pulmonary blood flow at an arteriolar level. In a meta-analysis published in 2019, RPVO as assessed with V/Q planar scintigraphy was associated with an increased risk of recurrent VTE. Although the analysis possibly lacked statistical power, RPVO was not predictive of recurrent VTE if it was assessed by CTPA [27]. Furthermore, CTPA has a higher radiation dose, especially to female breast, and requires the use of iodinated contrast media. Finally, the interpretation, comparison with previous scans, and quantification of RPVO are not simple with CTPA. In contrast, the interpretation of V/Q planar scintigraphy in the follow-up of PE does not require any particular expertise as it follows the same principles and semiological criteria as for the detection of acute PE, namely, the identification of mismatched perfusion defects.

In all studies that assessed RPVO as a predictor of VTE recurrence, RPVO was assessed with V/Q planar scintigraphy. However, a current limitation to the use of planar scintigraphy is high variability of RPVO definition in the literature. In some studies, lung planar scintigraphy was considered as abnormal if the RPVO was >5% [19], while in others, the cutoff was 10% [21] or 15% [22]. In a study including 65 participants for RPVO assessment with V/Q planar scintigraphy, κ coefficient for interobserver agreement between 2 nuclear medicine physicians was only 0.71 [24]. This might be explained by the inherent limitation of RPVO quantification using planar scintigraphy, which is only based on a visual estimation on 2-dimensional images.

Advances in imaging equipment and the development of radiotracers for ventilation have allowed the introduction of V/Q single photon emission computed tomography (V/Q SPECT/CT), a method of scintigraphic image acquisition that offers the advantage of 3-dimensional imaging, enabling more accurate quantification of RPVO [28]. V/Q SPECT/CT imaging may also open new perspectives for enabling automated quantification of RPVO. Importantly, V/Q SPECT/CT imaging, and not planar, is currently overwhelmingly used in daily practice in the follow-up of patients with PE [29].

### Study aims

1.2

The primary aim of this study is to assess whether RPVO, evaluated with V/Q SPECT/CT imaging, is an independent predictor of recurrent VTE in patients with PE. This will be assessed in patients for whom anticoagulation is currently discontinued, but for whom there is a need to better predict the risk of recurrence in clinical practice. This includes patients with PE provoked by a minor transient risk factor and patients with unprovoked PE for whom anticoagulation need not be prolonged, regardless of why anticoagulation is not continued (benefit–risk balance, treating physician’s decision, and patient’s preferences). Given its technical advantages over planar imaging and because it is currently widely used in daily practice, V/Q SPECT/CT imaging will be used for RPVO assessment.

We also aim to assess the usefulness of performing a V/Q SPECT/CT scan after 3 to 6 months of OAT in various clinical situations. RPVO is very common after 3 to 6 months of OAT, and postembolic sequelae have the same pattern as acute PE on V/Q imaging. Thus, we aim to assess the diagnostic utility of a reference V/Q SPECT/CT scan performed after 3 to 6 months of anticoagulation in case of suspicion of PE recurrence. Finally, up to 50% of patients present with postpulmonary embolism syndrome, which is defined as new or progressive dyspnea, exercise intolerance, or impaired functional status after at least 3 months of anticoagulation following acute PE. We aim to study those patients with persistent dyspnea and impaired quality of life (QoL) after PE and to assess the role of V/Q SPECT/CT imaging in this setting.

## Methods

2

### Objectives

2.1

The primary objective is to assess whether RPVO, evaluated with V/Q SPECT/CT imaging after completion of 3 to 6 months of anticoagulation, is an independent predictor of recurrent VTE in patients with PE. The secondary objectives are listed in Table.

**Table tbl1:** Primary and secondary objectives of the PRONOSPECT cohort study.

Primary objective	
	To assess whether RPVO, evaluated with V/Q SPECT/CT imaging after completion of 3-6 mo of anticoagulation, is an independent predictor of recurrent VTE in patients with PE.
Secondary objectives	
VTE recurrence	To assess the cumulative risk of VTE recurrence 1 y and 2 y after discontinuation of anticoagulant therapy.
	To assess predictors for recurrent VTE other than RPVO, in order to be able to derive a predictive score.
	To assess the performances of scores already established to predict the risk of recurrence in patients with unprovoked PE, in patients at an intermediate risk of recurrence.
RPVO	To assess the proportion of patients with RPVO on V/Q SPECT/CT imaging after completion of 3 to 6 mo of anticoagulation.
	To assess different RPVO threshold on V/Q SPECT/CT imaging to predict the risk of VTE recurrence at 2 y.
	To assess predictors of RPVO at diagnosis.
	To compare technegas and krypton, the ventilation agents used in the study, for the assessment of RPVO after completion of 3 to 6 mo of anticoagulation.
Diagnosis of PE recurrence	To assess the safety of ruling out the diagnosis of PE recurrence with V/Q SPECT/CT imaging, using a baseline V/Q SPECT/CT scan performed after completion of 3 to 6 mo of anticoagulation.
Functional evaluation and quality of life	To assess the proportion of patients with dyspnea after completion of 3 to 6 mo of anticoagulation.
	To assess the proportion of patients with impaired QoL after completion of 3 to 6 mo of anticoagulation.
	To assess the association between RPVO and dyspnea or impaired QoL.
	To assess the proportion of patients with CTEPH.
	To assess whether RPVO, assessed with V/Q SPECT/CT imaging after completion of 3 to 6 mo of anticoagulation, is an independent risk factor for CTEPH.
	To assess the proportion of patients with chronic thromboembolic pulmonary disease.
	To assess the overall mortality of all causes during the 24-month follow-up.

CTEPH, chronic thromboembolic pulmonary hypertension; PE, pulmonary embolism; QoL, quality of life; RPVO, residual pulmonary vascular obstruction; V/Q SPECT, ventilation/perfusion single photon emission computed tomography; VTE, venous thromboembolism.

### Study design

2.2

The PRONOSPECT trial is a prospective multicenter cohort study.

### Participants

2.3

Inclusion criteria are as follows:•Patients aged ≥18 years.•Those who experienced an objectively proven PE.•Those who have been treated initially with anticoagulant therapy for 3 to 6 uninterrupted months (180-210 days) and for whom anticoagulation will not be prolonged.

Noninclusion criteria are as follows:•Unwilling or unable to give written informed consent.•No social security affiliation.•Isolated DVT.•Other indication for long-term use of OAT (eg, atrial fibrillation and mechanic valve; preventing primary end-point assessment).•Life expectancy < 6 months (preventing primary end-point assessment).•Any patients for whom there is a high risk of recurrence and a strong indication to treat for longer than 6 months:-PE provoked by a major persistent factor, such as active malignancy or antiphospholipid antibody syndrome [30].-Recurrent unprovoked PE.•PE provoked by a major transient risk factor [30] in patients for whom there is a very low risk of recurrence and a strong indication to propose short duration of OAT.

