### Procedure

2.4

Once a patient has consented to participate, a standardized baseline patient assessment will be performed, including the following:•V/Q SPECT/CT imaging. Ventilation imaging will be performed using either ^81m^krypton gas or ^99m^Tc-technegas (Cyclomedica), an ultrafine particle that exhibits near-optimal distribution properties. These 2 ventilation agents allow for optimal ventilation SPECT acquisition [31,32]. V/Q SPECT/CT images should not be used for patients’ management.•Collection of other potential predictor variables for VTE recurrence:-Demographic characteristics and risk factors for VTE.-Lab tests including D-dimer testing, drawn prior to discontinuation of OAT to mimic actual practice.-Lower limb compression ultrasonography if the patient had an associated DVT.•Functional evaluation:-Dyspnea index using Modified Medical Research Council (MMRC) scale and New York Heart Association (NYHA) score.-Quality of life index using Pulmonary Embolism (PEmb)-Qol questionnaire.-Cardiac ultrasound in case of residual dyspnea or if the V/Q SPECT/CT demonstrates RPVO.

Patients will be included in the study the day of anticoagulation discontinuation and will be followed up in clinic or contacted by telephone every 6 months up to 2 years. Patients will be educated about the signs and symptoms of recurrent VTE and given emergency contact numbers and instructions if these signs were to arise in follow-up. In case of suspected PE recurrence, the diagnostic and therapeutic management will be left at the discretion of treating physician according to the availability of imaging modalities. When a V/Q SPECT/CT scan is performed, recurrent PE will be diagnosed is there is 1 segmental or 2 subsegmental new mismatched perfusion defects [33,34]. The study design is presented in Figure.

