### Sample size justification

2.7

The number of patients arises from comparison of the time to occurrence (censored by anticoagulation for another reason than recurrent VTE or loss to follow-up) of recurrent VTE, from the completion of anticoagulation. Based on the known recurrence risk of 4% to 7% at 1 year in patients at intermediate risk of recurrence and given that the study will also include patients with unprovoked PE whose recurrence risk is approximately 9% at 1 year, we estimated the recurrence risk in our population at 6% at 1 year (4% at 6 months and 8% at 2 years). Based on previous studies, we expect a VTE recurrence rate of 12% at 2 years in the group with RPVO (6% at 6 months) and 5% in the group without RPVO (2.5% at 6 months; hazard ratio, 2.5) [7,10,[31], [32], [33], [34]]. We anticipate that 10% of patients will be censored before 2 years (anticoagulation for another reason than recurrent VTE or loss to follow-up). We also expect that 40% of patients will have RPVO on V/Q SPECT/CT imaging, and 60% without RPVO. Thus, 52 events are required to ensure a power of 90%. Based on these assumptions, 655 patients need to be included.

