First, while there is currently no indication to prolong anticoagulation in patients with PE provoked by a minor transient risk factor, the decision to discontinue anticoagulation in some patients with unprovoked PE includes a significant subjective component and often involves various factors such as the estimated benefit–risk balance or the patient preference. This may have a direct influence on the study population’s inherent recurrence risk and homogeneity and limit the generalizability of findings. On the other hand, it is a pragmatic approach. The population corresponds to patients for whom there is a need to better predict the risk of recurrence. Similar population heterogeneity has been observed in other studies [37]. Furthermore, the population will be well documented at inclusion. Minor risk factors associated with PE and the reasons justifying the discontinuation of anticoagulant treatment in patients with unprovoked PE (patient preference, benefit–risk balance) will be collected. Thus, subgroup analyses could be conducted. Second, as patient’s management will not be based on RPVO or other potential predictors, this noninterventional study design will not allow us to assess the impact of modifying therapeutic management based on RPVO status. Furthermore, although performing a baseline V/Q scan after 6 months of anticoagulation could present various benefits, it remains a costly examination, with unequal accessibility, and is associated with exposure to radiation. One of the secondary objectives of the study is to assess predictors of RPVO. This may allow clinicians to target patients at increased risk of RPVO, who may benefit from a baseline V/Q lung scan, and, conversely, patients with a low risk of RPVO for whom the examination would not be justified. Finally, V/Q SPECT/CT scan performed at inclusion should remain available for interpretation of any suspicion of VTE recurrence. To limit a possible bias related to the knowledge of RPVO status, all suspicions of VTE recurrence (including the suspicion confirmed and ruled out) will be adjudicated blindly by an independent central Clinical Events Committee. Furthermore, to determine RPVO status, a central review of all V/Q SPECT/CT images will be performed independently by 2 nuclear medicine physicians who will be blinded to clinical history and the patient’s outcome. Any difference in interpretation will be resolved by consensus.

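### The inclusion criterion equates 3 to 6 months of anticoagulation with 180-210 days, a range that overlaps it by at most about 4 days and shuts out the 3-month stoppers the protocol expects

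*Protocol article*

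**What the plan says.** The protocol article states the duration of initial anticoagulation in several places.

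- **Section 2.3, Participants.** Eligible patients are those "treated initially with anticoagulant therapy for 3 to 6 uninterrupted months (180-210 days"), and for whom treatment will not be extended. This is the only place where a range in days appears. The same section excludes patients with "a strong indication to treat for longer than 6 months".
- **Abstract, Methods.** Participants are patients "who have been treated with anticoagulant therapy for 3 to 6 uninterrupted months", with no range in days. The abstract adds: "Anticoagulants will be withdrawn at the 3- or 6-month points from diagnosis".
- **Section 2.1, Objectives.** Residual pulmonary vascular obstruction (RPVO), the primary predictor, is "evaluated with V/Q SPECT/CT imaging after completion of 3 to 6 months of anticoagulation". The abstract's objectives and section 1.2 (Study aims) use the same 3-to-6-month wording.
- **Section 2.4, Procedure.** "Patients will be included in the study the day of anticoagulation discontinuation". The baseline assessment, including the scan, belongs to this point in the patient's course.
- **Section 3, Discussion/Limitations.** A remark on cost, access and radiation speaks of "performing a baseline V/Q scan after 6 months of anticoagulation".

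**The concern.** A parenthesis placed directly after a duration normally restates it in other units. Here the restatement starts where the stated duration ends. A patient who stops at the 3-month point satisfies the words and fails the days. A patient who stops at, say, day 200 satisfies the days and exceeds the words.

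This is an operative eligibility rule in a multicenter cohort. It decides who may enter and, because the scan is done at the end of this treatment period, it also decides when RPVO is measured. If the day range were the rule in force, the cohort would consist of patients treated for roughly six to seven months, and the primary objective would describe a treatment period that almost none of them had. The article says that the study commenced in June 2024, so enrolment may already be under way with this criterion.

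**Working it through.** **Inputs.** From section 2.3: 3 to 6 months, and 180-210 days. From the abstract: withdrawal at 3 or 6 months from diagnosis. The article does not define a month in days, so three conventions are tried.

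**Step 1: can the stated day range be reproduced from the months?**

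| Convention | 3 months | 6 months |
|---|---|---|
| 30-day month | 3 × 30 = 90 | 6 × 30 = 180 |
| 365.25/12 = 30.44-day month | 91.3 | 182.6 |
| Widest calendar range | 89 (shortest) | 184 (longest) |

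None gives 180-210. The lower limit is about twice what it should be, and the upper limit is 26 to 30 days too high (210 − 184 = 26; 210 − 180 = 30).

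**Step 2: the reverse conversion.** 180/30.44 = 5.9 months and 210/30.44 = 6.9 months. With 30-day months the range is 6.0 to 7.0.

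**Step 3: overlap of the two ranges.**

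| Convention | Overlap | Share of the 3-6 month range | Share of 180-210 days |
|---|---|---|---|
| 30-day month | day 180 only | about 0% | about 0% |
| 30.44-day month | 182.6 − 180 = 2.6 days | 2.6/91.3 = 2.9% | 2.6/30 = 8.8% |
| Widest calendar range | 184 − 180 = 4 days | 4/95 = 4.2% | 4/30 = 13.3% |

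**Step 4: the two planned stopping points against the day range.**

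- 3-month point, about day 90: 180 − 90 = 90 days short of the lower limit, so not eligible under the day range.
- 6-month point, day 180 to about day 184: inside the day range, and within 6 months if the months are counted generously enough. These patients can meet both rules.
- Days 185 to 210: inside the day range, but beyond 6 months under every convention.

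**Step 5: does the conflict reach the sample size?** Section 2.7 states that "52 events are required to ensure a power of 90" percent, from a hazard ratio of 2.5 and a 40:60 split. With Schoenfeld's formula and a two-sided 5% level (assumed, since the article gives none), events = (1.960 + 1.282)² / (0.4 × 0.6 × (ln 2.5)²) = 10.51 / 0.2015 = 52.1. This is 52 to the nearest whole number, or 53 rounded up, and 52 events give 89.9% power. Treatment duration is not an input, so the event count stands whichever window is intended.

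**The case against.** The best defence is that 180-210 days is a visit window for patients who stop at 6 months: a 30-day band starting at day 180 looks like one. The sentence does not say so, because the parenthesis follows the whole phrase about 3 to 6 months and no other section explains it. On that reading the 3-month stop has no window at all, so the criterion would still need correcting.

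It can also be said that one parenthesis is the outlier, since the abstract, the aims, the objectives and the words of the criterion itself all say 3 to 6 months. That is so, and it keeps the defect narrow. The Discussion wording is a passing remark rather than a scheduling rule and adds little weight. The mention of treatment beyond 6 months among the exclusions concerns indication, not days received, and does not settle the matter.

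Several stronger readings are tempting, but the article does not support them:

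- **That the two rules select almost disjoint populations.** It is the day intervals that barely overlap. Withdrawal is planned at two points, so durations should cluster there, and patients who stop at the nominal 6-month point can meet both rules. The split of patients is not given.
- **That sites will mix populations because of this sentence.** Enrolling both 3-month and 6-month stoppers is the declared design. Sites work from the full protocol, which is not shown, so how they apply the criterion is unknown.
- **That the assumed 40% prevalence or the event rates become invalid.** Section 2.7 ties neither to treatment duration.
- **That the article's Conclusion is undermined.** The Conclusion in the abstract states no duration. The wording at risk is that of the primary objective.

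**Conclusion.** The criterion is wrong as written. Under no month convention do 3 to 6 months equal 180-210 days, and the shared stretch runs from the single day 180 to about 4 days. Taken literally, the day range excludes every patient who stops at the 3-month point, contrary to the abstract and the primary objective, and admits patients up to about four weeks beyond 6 months.

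What is affected is eligibility, the timing of the RPVO measurement and, if the day range is enforced, the match between the primary objective and the cohort. Follow-up starts on the day of discontinuation under either reading, and the form of the primary Cox comparison does not change. The number of patients on each side cannot be worked out from the article. The 52 events, 655 patients and 40% prevalence are not shown to be affected.

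The conclusion rests only on unit conversion and on reading the parenthesis as a restatement of the words before it. The article does not settle which window is intended.

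**What to change.** Reconcile section 2.3 with the abstract's Methods and with section 2.1, and align the Discussion wording, so that months and days agree for each stopping point that is eligible. The sponsor decides which window is intended; nothing in the article allows a reviewer to choose. If more than one stopping point is eligible, give each its own range in days. Notify sites of the corrected criterion.

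Record the actual number of days of anticoagulation at the scan. Section 2.4 does not list this explicitly among the baseline variables, so confirm that the case report form captures it. If more than one stopping point stays eligible, a sensitivity analysis of the primary Cox model adjusted for that duration is an optional addition.

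The cost is a wording amendment, a site notice and, at most, one recorded variable. The sample size calculation does not need to be redone on this account.
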